### Sample size

The sample size was calculated based on the estimated effect size of the change in interpretation bias before and after a CBM-I intervention (*d* = .43) according to a recent meta-analysis on the field [20]. Following G*Power calculations [39], the minimum sample size (*α* set at 0.05, power at 0.95) to find a difference in a repeated-measures multivariate analysis of variance with one within-subjects factor (two-time points) and one between-subjects factor (two groups) was 73 participants. Due to expected attrition [40], 20% more participants will be recruited, reaching a total sample size of 88 participants.

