### Cognitive bias measures

#### Ambiguous Scenarios Test for Depression-II

The AST-D-II [48] is a self-report measure of interpretation biases. It consists of 15 ambiguous scenarios which participants have to rate on a scale from −5 (very unpleasant) to 5 (very pleasant). Participants are asked to imagine each scenario as vividly as possible and as if it was happening to them (e.g. *As you enter the room, the commission welcomes you and begins with the oral examination. After just a few minutes you know intuitively how the examination will go*). Two parallel versions are used in counterbalanced order at baseline, post-treatment, and follow-ups. Participants’ responses to the items were transformed into a total sum score by adding up the values of each item, rescaled from 1 to 11 (higher scores represent more positive interpretations). Internal consistency is good (*α* = 0.87) for the general scale and also for its two short versions A (*α* = 0.77) and B (*α* = 0.78).

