### Analytic plan

Demographic data and pre-treatment measures will be analysed to test for group differences with analysis of variance and chi-squared test for nominal variables.

Complete case analyses will be conducted for those participants who complete all 4 online sessions and attend pre- and post-assessment evaluation sessions. A series of 2 (group: experimental, control) × 3 (symptom group: never, present, past) × 2 (time: pre-training, post-training) analyses of variance will be performed to evaluate the change between groups. The symptom group will be created based on present and past symptoms of depression and/or anxiety to explore their influence on the results. Intention-to-treat (ITT) analyses will be conducted with all participants, regardless of session or outcome measure completion. ITT mixed models (restricted maximum likelihood (REML) estimation) will be used to account for missing data [71]. Binary logistic regression will be used to evaluate the assumption that data is Missing at Random (MAR). Exploratory mediation analyses will be conducted to study the interplay between the different cognitive bias scores given the change of the intervention. Finally, follow-up assessments will be included in a series of analyses of variance to evaluate group differences in time. All analyses will be performed in SPSS Statistics 20 with an *α* level of 0.05.

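### AST-D-II form order is counterbalanced by design but absent from the stated ANOVA, so any mean difference between the two versions costs precision for that outcome

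*Protocol article*

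**What the plan says.** The section on the Ambiguous Scenarios Test for Depression-II states: "Two parallel versions are used in counterbalanced order at baseline, post-treatment, and follow-ups". The evidence it offers on the versions is internal consistency, given for the general scale (0.87) "and also for its two short versions A" (0.77) and B (0.78). It reports no mean difference between A and B, and does not say whether order is balanced within each arm.

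The Analytic plan sets out the pre-post model for the complete-case analysis with its factors and levels: "A series of 2 (group: experimental, control) × 3 (symptom group: never, present, past) × 2 (time: pre-training, post-training) analyses of variance will be performed". Form and form order are not among them. For the intention-to-treat analysis it says that "ITT mixed models (restricted maximum likelihood (REML) estimation) will be used to account for missing data", without listing the fixed effects. Follow-up data go into further analyses of variance whose factors are not itemised.

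The Sample size section rests on the "estimated effect size of the change in interpretation bias before and after a CBM-I intervention", d = 0.43, and on a model "with one within-subjects factor (two-time points) and one between-subjects factor (two groups) was 73 participants". That model has no order factor either.

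**The concern.** Counterbalancing two versions keeps a difference in their difficulty out of the average change. It does not keep it out of the scatter. A participant who goes from the version that scores lower to the one that scores higher shows an upward shift of delta. A participant in the reverse order shows the same shift downward. Unless the model knows the order, these opposite shifts count as unexplained variation in the group-by-time test.

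The AST-D-II is one of two interpretation-bias measures in the article (the other is the sentence index from the MCAT) and the only one repeated at 2 weeks and 3 months. The first hypothesis concerns interpretation bias. What is at stake is the width of the interval and the power for this one outcome. The source of variation is created by the design and can be removed in the analysis.

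**Working it through.** **Inputs from the article.** d = 0.43, alpha 0.05, power 0.95, two groups at 1:1, two time points, minimum N = 73, recruitment target 88. **Assumed, because not given:** rho = 0.5 (0.7 as a second case); delta from 0.1 to 0.5; each participant takes A then B, or B then A, at pre and post.

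**1. The plan's own figure.** Take f = d/2 = 0.215 and the noncentral F test of the group-by-time interaction with lambda = f² × N × 2/(1-rho).

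- lambda = 0.215² × 73 × 2/0.5 = 0.046225 × 292 = 13.50, on 1 and 71 degrees of freedom.
- Power = 0.952, and 73 is the smallest N that reaches 0.95. The stated figure reproduces.

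**2. Effect of leaving order out.** Measure the score in SD units. With order modelled, Var(change) = 2(1-rho), which is 1 at rho = 0.5. With order omitted and the two orders equally common, the shift of +delta or -delta adds delta². The variance factor is 1 + delta²/[2(1-rho)], and lambda is divided by it. At rho = 0.5:

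| delta | variance factor | lambda at N = 73 | power at N = 73 | N for 95% power |
|---|---|---|---|---|
| 0.1 | 1.01 | 13.36 | 0.950 | 73 |
| 0.2 | 1.04 | 12.98 | 0.944 | 76 |
| 0.3 | 1.09 | 12.38 | 0.935 | 79 |
| 0.4 | 1.16 | 11.64 | 0.920 | 84 |
| 0.5 | 1.25 | 10.80 | 0.900 | 90 |

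At rho = 0.7 the base variance is 0.6. The factors are 1.067, 1.15 and 1.417 at delta = 0.2, 0.3 and 0.5. With the standardised effect held, power is 0.939, 0.922 and 0.861.

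**3. With order in the model.** One error degree of freedom is spent (70 instead of 71). Power at N = 73 stays at 0.952 whatever the value of delta.

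**4. Level of the unadjusted test.** Simulation: 40,000 runs per setting, N = 76, rho = 0.5, symptom group left out.

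- Order assigned without regard to arm: type I error between 0.048 and 0.053.
- Order balanced exactly within arm: type I error 0.046, 0.039 and 0.027 at delta = 0.2, 0.3 and 0.5. The group difference then carries no form variance, but the estimated error still does, so the test is conservative.

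The powers in step 2 describe order assigned without regard to arm. With exact balance the simulated loss is smaller: 0.956, 0.950 and 0.933 unadjusted at delta = 0.2, 0.3 and 0.5, against 0.955 to 0.957 adjusted (N = 76).

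**5. Chance imbalance of order between arms.** With n per arm, the difference between arms in the share given one order has variance 2 × 0.25/n, and it moves the group difference in change by 2 × delta × that difference. The variance contributed is 4 × delta² × 0.5/n = 2 × delta²/n. The extra delta² in step 2 contributes delta² × 2/n to the variance of the group difference, which is the same quantity.

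**The case against.** The strongest objection is that this is a detail for the analysis plan. The Analytic plan gives one generic line for a series of outcomes, only one of which has parallel versions, and a nuisance term for a single instrument would not be expected there. This stands for the mixed models, whose fixed effects are not listed: form cannot be called missing from them. It stands less well for the ANOVA, which is written as a closed factorial with levels and already includes one exploratory factor. Run as written, that model omits a design factor.

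Second, the loss is hypothetical. The versions are described as parallel, no difference between them is reported, and at rho = 0.5 the loss is under 2 power points up to delta = 0.3. This stands and sets the size of the point. Nearly equal alphas do not settle it, because internal consistency says nothing about equality of means.

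Third, the baseline is a choice. Nothing says that the effect size from the meta-analysis excludes form variance. If the 95% already includes it, adjustment raises power above the plan instead of restoring it. The variance factor is the same either way.

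Fourth, neither the hypothesis nor the sample size names the AST-D-II. That also stands, and limits the point to one outcome.

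A reader might infer more: that unequal orders bias the comparison of arms, as a harm on top of the lost precision. The document does not support this. The imbalance has zero expectation and, by step 5 of the working, is the same variance counted again; the unadjusted standard error already covers it. The complete-case rule requires all four online sessions, which only the experimental arm receives before the post-assessment, so exclusions may upset an exact balance. A systematic shift would still need losses that depend on form order differently in the two arms, and nothing in the article suggests that.

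**Conclusion.** The point holds as a minor improvement in efficiency for the AST-D-II. The stated ANOVA omits a factor that the design creates, and any mean difference between versions enters the error of the group-by-time test as delta². At N = 73 and rho = 0.5 the cost is about 0.8 power points at delta = 0.2, 1.7 at 0.3, 3.2 at 0.4 and 5.2 at 0.5. It is larger at rho = 0.7, and smaller if order is balanced exactly within arm. All of this depends on an assumed delta and rho. If the versions have equal means, nothing is lost.

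The unadjusted test remains valid, the stated 73 reproduces on the assumptions shown, and no figure in the article is wrong on this account. Whether d = 0.43 was converted properly for the sample size is a separate question and plays no part in this conclusion.

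**What to change.** For the AST-D-II only:

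- **Pre-post ANOVA:** add form order (AB or BA) as a between-subjects term together with its interaction with time, and report the order-adjusted group-by-time effect. Do not cross order with group and symptom group. Full crossing would give 2 × 3 × 2 = 12 between-subject cells in place of 6, and would cost six degrees of freedom instead of one.
- **Mixed model and follow-up analyses:** include the form used at each visit (A or B) as a fixed effect.
- **Wording:** one sentence naming these terms, and one stating whether order was balanced within arm.

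The cost is about one error degree of freedom and no new data collection, provided the form given at each visit was kept. The article does not say so, but the baseline questionnaires were completed on an online platform, so it should be recoverable. If the versions prove equal, the degree of freedom is all that is spent.

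### The 2 × 3 × 2 ANOVA tests change scores and crosses in a symptom factor the sample size left out; a baseline-adjusted comparison would be more precise on the same data

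*Protocol article*

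**What the plan says.** Under Analytic plan, the complete-case analysis covers participants who finish all four online sessions and attend both assessments. For them a series of three-factor models is planned: group (experimental, control), "3 (symptom group: never, present, past") and time (pre, post). These "analyses of variance will be performed to evaluate the change between groups". The symptom factor is there to explore how present or past depression or anxiety affects the results. It is formed from PHQ-9 and GAD-7 cut-offs completed before the intervention (Symptom measures).

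The same section plans intention-to-treat mixed models fitted by REML on all participants, without saying how baseline enters them. It closes with "All analyses will be performed in SPSS Statistics 20 with an *α* level of 0.05" and does not state the type of sums of squares.

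The Sample size section uses d = 0.43, described as the "estimated effect size of the change in interpretation bias before and after a CBM-I intervention", with α = 0.05 and power 0.95. It names a design with "one within-subjects factor (two-time points) and one between-subjects factor (two groups) was 73 participants". After allowing for attrition, "20% more participants will be recruited, reaching a total sample size of 88 participants". No symptom factor enters the calculation. Randomisation and blinding describes 1:1 allocation and no stratification.

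**The concern.** There are two separate losses of precision on the main question.

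First, when time has only pre and post as levels, the group-by-time interaction is algebraically the between-group comparison of change scores. In a randomised comparison that estimator is valid, but it is less precise than a comparison of post scores adjusted for baseline whenever the pre–post correlation is below 1. The baseline value is already collected.

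Second, in a model with all interactions, the Type III group-by-time test (the SPSS default) is an equally weighted average of three symptom-specific effects. If one symptom group is small, its imprecise effect still carries one third of the weight. The sample size made no allowance for this. The three-way term itself would rest on at most about 12 people per cell (73/6) to 15 (88/6), even with equal groups.

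The trial is small, so power lost through the form of the model matters, and most of it can be recovered without recruiting anyone.

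**Working it through.** **Inputs from the protocol.** α = 0.05, power 0.95, d = 0.43, two groups, two times, N = 73 before attrition, 1:1 allocation. **Assumed, because the protocol gives no value:** the pre–post correlation ρ; the symptom-group shares; two-sided tests; equal variances at pre and post; Type III sums of squares.

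**1. Reproduce the stated 73.** For the group-by-time F test, λ = N·f²·m/(1−ρ) with df 1 and N−2. Take f = d/2 = 0.215, m = 2 and ρ = 0.5:
- N = 73: λ = 73 × 0.215² × 2/0.5 = 13.50, power 0.952.
- N = 72: power 0.949.

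The minimum is 73, as stated. A multivariate form with f(V) = 0.43 also gives 73. Both calculations are for a 2 × 2 design, so the symptom factor was not included.

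**2. What effect that implies.** Let D be the between-group difference in change, in SD of a single measurement. Then λ = N·D²/[8(1−ρ)]. Equating this with step 1 gives D = 4f = 0.86. If instead 0.43 SD is itself the between-group difference in change, D = 0.43. Both are carried forward.

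**3. Change score against baseline adjustment.** In units of the measurement variance:
- change score: 2(1−ρ)
- post score adjusted for baseline: 1−ρ²
- ratio: (1−ρ²)/[2(1−ρ)] = (1+ρ)/2

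| ρ | 0.3 | 0.5 | 0.7 | 0.9 |
|---|---|---|---|---|
| variance ratio | 0.65 | 0.75 | 0.85 | 0.95 |

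Adding baseline and two symptom indicators uses three more degrees of freedom. The critical t moves from 1.994 (71 df) to 1.995 (68 df), which is negligible.

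**4. Power at N = 73, ρ = 0.5.** The adjusted model has λ = N·D²/[4(1−ρ²)].

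| D | change score, 2 × 2 | baseline-adjusted, symptom group additive |
|---|---|---|
| 0.86 | λ = 13.50, power 0.952 | λ = 18.00, power 0.987 |
| 0.43 | λ = 3.37, power 0.44 | λ = 4.50, power 0.55 |

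For D = 0.86, the adjusted model reaches 95% power with 55 people instead of 73.

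**5. Crossing with the symptom factor.** With shares p₁, p₂, p₃, the variance of the equally weighted group-by-time effect is multiplied by (1/9)·Σ(1/pₖ):
- equal thirds: (3+3+3)/9 = 1.00
- 50/30/20: (2+3.33+5)/9 = 1.15
- 70/20/10: (1.43+5+10)/9 = 1.83

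Power of that change-score test at N = 73, ρ = 0.5:

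| assumed shares | D = 0.86 | D = 0.43 |
|---|---|---|
| equal thirds | 0.952 | 0.44 |
| 50/30/20 | 0.922 | 0.39 |
| 70/20/10 | 0.764 | 0.27 |

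In terms of precision, 73 people act like 73/1.148 = 64 at 50/30/20 and 73/1.825 = 40 at 70/20/10.

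**The case against.** The planned ANOVA is not wrong. In a randomised comparison the change-score test is valid, so the complaint is about efficiency. That is fair, and it limits how serious the point is.

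A reader might infer four stronger things that the documents do not support:
- **That the symptom groups are known to be unbalanced.** No shares are given. Open entry for any interested adult student, groups formed by cut-offs and no described stratification make inequality likely, but its size is unknown. At equal thirds the crossed model costs nothing. The loss also presumes Type III sums of squares, which the protocol does not specify.
- **That the trial is underpowered on its own terms.** The 0.44 follows only if 0.43 SD is read as the between-group difference in change. On the reading that reproduces 73, the stated power is met.
- **That the whole analysis has these weaknesses.** The intention-to-treat REML models are also planned. They are not said to carry the 2 × 3 × 2 structure, and their baseline handling is unstated. The losses are shown only for the complete-case ANOVA.
- **That the change is free.** Using symptom group only as a covariate removes the interaction through which the plan explores symptom status, so that term has to be kept elsewhere.

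Two further objections stand in part. The complete-case set requires completion of all four sessions, which selects after randomisation in the experimental arm. There, equal baseline means cannot be assumed, and ANCOVA and change scores may estimate different quantities. Also, Trial status gives completion by 30 December 2020 and the article appeared on 31 July 2021, so any change to the main model comes late. Neither removes the gain in the analysis of all randomised participants; they determine where each model belongs and how the change is reported.

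**Conclusion.** The point holds as an avoidable loss of precision and a mismatch between the design that was sized (2 × 2) and the analysis that is planned (2 × 3 × 2). It is not an invalid test.

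The direction of the baseline-adjustment gain is certain for any ρ below 1 under randomisation with equal pre and post variances. Its size is not: variance falls by 35% at ρ = 0.3 and by only 5% at ρ = 0.9. The extra loss from the crossed symptom factor is conditional on unequal shares and a Type III test, and ranges from nil to an 83% increase in variance over the shares shown. The change is worth making under either reading of d = 0.43.

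**What to change.** - **Main contrast, each outcome:** compare post scores between arms, adjusted for the baseline value, with symptom group as an additive covariate. Symptom group is measured before the intervention, so it is a legitimate covariate.
- **Intention-to-treat analysis:** use the planned REML mixed model on all randomised participants, with baseline means constrained equal across arms, and state this.
- **Completer analysis:** use ANCOVA without relying on the equal-baseline constraint, and note that this set is selected after randomisation.
- **Symptom interaction:** keep group × symptom × time as a separate model labelled exploratory, with cell sizes reported.
- **Sample size text:** say that 73 was calculated for a 2 × 2 design without the symptom factor.

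The cost is small. No new data are needed, and the symptom exploration is kept as a secondary model. Because the analysis is already published and the trial is complete, the change and its date must be documented; showing the published ANOVA alongside would let readers see its effect.

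### Logistic regression of missingness cannot evaluate the missing-at-random assumption behind the intention-to-treat model, so the planned check could give false reassurance

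*Protocol article*

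**What the plan says.** All of this is in the Analytic plan of the protocol article. The intention-to-treat set is everyone: "Intention-to-treat (ITT) analyses will be conducted with all participants, regardless of session or outcome measure completion". These data are analysed with mixed models fitted by REML, which "will be used to account for missing data". The next sentence gives the check on the assumption behind that model: "Binary logistic regression will be used to evaluate the assumption that data is Missing at Random (MAR"). The text names no covariates for this regression and no rule for acting on its result.

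The other analysis set is completers: "Complete case analyses will be conducted for those participants who complete all 4 online sessions and attend pre- and post-assessment evaluation sessions". The Sample size section expects attrition and raises the target from 73 to 88.

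**The concern.** The article names a method and gives it a purpose that the method cannot serve. MAR says that, given what was observed, the chance of a missing score does not depend on the score itself. A regression that contains only observed variables does not address that statement.

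- If observed variables predict missingness, MCAR is contradicted, but MAR may hold perfectly well.
- If they do not, MCAR is not contradicted, but missingness may still depend on the unseen post-intervention score.

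The REML model is the plan's only stated protection against missing outcomes, and it is valid under MAR. The completer analysis is no cross-check, because it is exposed to the same selection. If dropout did depend on unseen response, a reader who took the regression as evidence for MAR would place unwarranted trust in a biased treatment effect.

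**Working it through.** **1. The plan's own figure.** From the Sample size section: d = 0.43, α = 0.05, power 0.95, two groups, two time points. The article gives no pre-post correlation, so ρ = 0.5 is assumed.

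- f = d/2 = 0.215
- λ = f²·N·m/(1 − ρ) = 0.046225 × 73 × 2/0.5 = 13.50, with 1 and 71 degrees of freedom
- Power is 0.952 at N = 73 and 0.949 at N = 72, so 73 reproduces.
- 73 × 1.2 = 87.6, rounded up to 88.

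This point disputes neither number. They fix the size of the simulated trial, and ρ = 0.5 is the value that returns 73 (ρ = 0.3 gives 101 and ρ = 0.7 gives 45).

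**2. What the regression can see.** Write y₀ for baseline, y₁ for post-intervention, g for arm.

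- MAR requires P(y₁ missing | g, y₀, y₁) = P(y₁ missing | g, y₀).
- The check fits logit P(y₁ missing) = a + b₁g + b₂y₀ and tests b₁ = b₂ = 0.

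That null hypothesis is a consequence of MCAR, not of MAR. A coefficient on y₁ would be needed to test MAR, and y₁ is absent for exactly the people in question. More observed covariates do not change this.

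**3. Does the check separate the cases?** Simulated trials of 88, allocated 1:1, with y₁ = 0.5y₀ + 0.43g + e and SD(e) = √(1 − 0.25) = 0.866. About 20% of y₁ is missing. The check is a likelihood-ratio test on arm and baseline at 0.05. The effect is estimated by baseline-adjusted regression on observed post scores, as a stand-in for the mixed model.

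| Mechanism | Check significant | Mean estimate (true 0.43) |
|---|---|---|
| MCAR | 5% | 0.43 |
| MAR, through baseline | 88% | 0.42 |
| MNAR, through post score, experimental arm only | 13% | 0.57 |
| MNAR, through post residual, opposite directions in the two arms | 6% | 0.70 |

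The check is significant most often where MAR holds and the estimate is essentially unbiased. It is seldom significant where MAR fails.

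**4. Range over the strength and form of dependence.** Dropout depends on poor response in the experimental arm only: logit P(missing) = −1.55 − s·g·(departure from expected response). At s = 0 this gives 1/(1 + e^1.55) = 17.5% missing. Over the settings used, missingness is about 18-21%. The departure is taken either as raw gain (post minus pre, less 0.43) or as the residual independent of baseline.

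| s (odds ratio per unit, eˢ) | Mean estimate | Check significant |
|---|---|---|
| 0.25 to 0.5 (1.3 to 1.6) | about 0.45 to 0.50 | low end of the 5-26% range |
| 1.0 (2.7) | about 0.55 to 0.57 | 6% (residual), 13-15% (raw gain) |
| 1.5 (4.5) | about 0.64 to 0.65 | 9% (residual), 23-26% (raw gain) |

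Across these settings the check is significant in about 5-26% of trials and the estimate is about 0.45-0.65 SD. Relative to the true value, 0.45/0.43 = 1.05 and 0.65/0.43 = 1.51, so it is about 5% to 51% too large.

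**The case against.** The strongest reply is that only one sentence is wrong. A REML mixed model is a standard choice that is valid under MAR, whatever this regression shows. Running a logistic regression of missingness is also good practice if it is used to find predictors. Both statements are right. The analysis is not condemned, but the stated purpose of the check still is.

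Three stronger readings are tempting, and the article does not support them.

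- *A biased estimate would be passed as sound.* A reader might infer this, but the article gives no pass/fail rule and does not say that a non-significant result licenses the model. False reassurance is possible, not certain, and it does harm only if dropout is MNAR.
- *The plan has no analysis that relaxes MAR.* None is named, but this is a condensed article, and such an analysis is commonly left to a fuller plan. Its absence is not the ground of this point.
- *Participants who do not benefit will drop out.* This is an assumption. The article describes features that work against it: course credits, monitoring of session completion, reminders for both groups, and access to the programme for controls right after the second assessment. Stopping sessions is also not the same as lacking an outcome.

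It can also be said that the simulated check is narrower than the data allow. The trial records mood around each session, credibility and expectancy, and session completion on the platform. Such variables could make MAR more plausible if they enter the model. They still would not let a regression test it.

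**Conclusion.** The point stands as an error in what the article says the analysis does. Logistic regression of missingness can speak against MCAR and find predictors of dropout. Its result neither supports nor refutes MAR.

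How much this matters depends on why outcomes are missing, which the article cannot tell us. Under weak dependence on response the overstatement is small, about 0.02 SD (0.45 − 0.43). Under strong dependence it reaches about 0.22 SD (0.65 − 0.43). Even in the setting where the check does best, it is silent in about three-quarters of trials (100% − 26% = 74%). These figures rest on an assumed correlation of 0.5, about 18-21% missing, one-sided dropout in the experimental arm, a check on arm and baseline only, and a regression stand-in for the mixed model. They illustrate the problem and do not predict the bias in this trial. No stated figure in the article changes. The sentence should be corrected.

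**What to change.** 1. Reword the sentence so that logistic regression is used only to identify predictors of missingness, for example arm, baseline AST-D-II, baseline DASS-21 and symptom group. Do not describe it as evaluating MAR.
2. Include those predictors in the REML model, so that MAR is assumed conditional on them.
3. Assess departures from MAR with a delta-adjusted (pattern-mixture) sensitivity analysis. Shift the missing experimental-arm post-intervention scores in the unfavourable direction, from no shift up to loss of the whole estimated effect, and report the shift at which the conclusion changes. If a fuller plan already contains such an analysis, cite it here.

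The Trial status section says the study was completed by December 2020, so this concerns analysis and reporting only. It costs a change of wording and a small amount of extra analysis on data already collected, with no new data and no change to the sample size.

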**Fig. 4 Fig4:**
[figure not shown]
Schedule of enrolment, interventions, and assessments

After completion of the three lab tasks, participants in the experimental group will receive in their email the link to complete the online programme from home. They will need to log in to an online platform created for this study and will be invited to create their own account and password to access the materials. Information will be stored solely using the participant’s code number and only the main researchers will have access to the data. These data will be recorded in the database of the platform and will be used by the researchers to monitor if participants in the experimental group complete all four online sessions before the post-intervention evaluation. When participants first access the platform, they will find only the first session available. Access to the next session will be granted only 24 h after completing the previous one. This intermission between sessions aims to enhance participants’ processing of the contents of each session as well as to avoid cognitive overload and boredom.

After finishing the 4-session training programme, participants in the experimental group will be notified again, after approximately 10 days, for a second assessment session. The control group will be allowed to complete the intervention right after the second assessment. To improve adherence, both groups will receive a reminder for the second assessment session the day before. Finally, participants will be sent the follow-up questionnaires (AST-D-II, DASS-21, PHI, SE) twice (in the next 2 weeks and 3 months). To increase adherence during the follow-ups, participants will be sent up to a maximum of three reminders to complete questionnaires. Both groups will have the opportunity to complete a ‘feedback question’ to give their opinion about the intervention. This question will be included in the post-assessment for the experimental group and at the follow-ups for the control group.

The procedure has been approved by the university ethics committee (Ref. 2018/19-017) and has been registered (ClinicalTrials.gov NCT03987477). Moreover, it follows the recommendations for a clinical trial protocol [70].

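### The 2-week and 3-month assessments are assigned only to analyses of variance on responders, although the same section adopts REML mixed models to handle missing data

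*Protocol article*

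**What the plan says.** The Analytic plan section of the protocol article names three sets of outcome analyses.

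- **Complete-case, pre-post.** "Complete case analyses will be conducted for those participants who complete all 4 online sessions and attend pre- and post-assessment evaluation sessions". These are ANOVAs with group, symptom group and time (pre, post) as factors.
- **Intention-to-treat.** "Intention-to-treat (ITT) analyses will be conducted with all participants, regardless of session or outcome measure completion", and "ITT mixed models (restricted maximum likelihood (REML) estimation) will be used to account for missing data". The missing-at-random assumption is to be examined by logistic regression.
- **Follow-up.** A separate closing sentence: "follow-up assessments will be included in a series of analyses of variance to evaluate group differences in time". No mixed model, imputation or other treatment of missing data is attached to it.

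The software is fixed: "All analyses will be performed in SPSS Statistics 20".

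The Procedure section says that "participants will be sent the follow-up questionnaires (AST-D-II, DASS-21, PHI, SE) twice (in the next 2 weeks and 3 months"), by email, and foresees some non-response: "To increase adherence during the follow-ups, participants will be sent up to a maximum of three reminders to complete questionnaires". It also lets the control group take the programme immediately after the second assessment. Under Objectives and hypotheses, maintenance over time is described as something to be explored.

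**The concern.** The plan accepts that missing data matter, works under missing-at-random and names a method that uses that assumption. For the emailed follow-up waves it then names a method that cannot use it. ANOVA takes no information from a participant's earlier scores when a later one is absent.

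The maintenance result would therefore describe those who answered, while the intention-to-treat pre-post result describes everyone randomised. A difference between the post-intervention and 3-month findings could reflect a change in who is analysed as well as a change in effect. If answering depends on how people have been scoring or improving, the follow-up estimate can also be biased.

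**Working it through.** **Starting number.** Inputs from the Sample size section: d = 0.43, so f = 0.43/2 = 0.215; α = 0.05; power 0.95; two groups, m = 2 time points. The correlation ρ between time points is not given; 0.5 is assumed. For the group-by-time interaction, λ = N·f²·m/(1 − ρ) = 73 × 0.046225 × 2/0.5 = 13.50, with 1 and 71 degrees of freedom. Power is 0.952, and 73 is the smallest N that reaches 0.95, so the stated figure reproduces. Then 73 × 1.20 = 87.6, rounded up to 88. This calculation covers pre and post only; follow-up is not part of it.

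**How many remain.** Losses at post, 2 weeks and 3 months are assumptions. Each loss applies to those still present, and those who leave do not return.

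| Assumed losses | In all four waves | In pre, post and 2 weeks |
|---|---|---|
| 10/10/10% | 88 × 0.90 × 0.90 × 0.90 = 64.2 | 88 × 0.90 × 0.90 = 71.3 |
| 17/10/15% | 88 × 0.83 × 0.90 × 0.85 = 55.9 | 88 × 0.83 × 0.90 = 65.7 |
| 17/15/25% | 88 × 0.83 × 0.85 × 0.75 = 46.6 | 88 × 0.83 × 0.85 = 62.1 |

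A single four-level ANOVA would use the middle column throughout. Separate ANOVAs would use the right-hand column at 2 weeks and, with this dropout pattern, the same middle column at 3 months.

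**What selective dropout does.** Illustrative large-sample simulation: equal correlation 0.6 between waves, higher score better, true maintained difference 0.43 SD, the three loss patterns above, selective dropout in the experimental arm only with a logistic slope of 1. Two contrasts were taken in those who remained: the group difference in change from pre to 3 months, and the raw group difference at 3 months.

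| Who leaves more often | Change contrast | Raw 3-month difference |
|---|---|---|
| Those with a poor last score | about 0.38 to 0.40 (0.37 in some runs with the heaviest loss) | 0.59 to 0.71 |
| Those with little pre-post improvement | 0.50 to 0.56 | about 0.43 |
| Unrelated to scores | 0.43 | 0.43 |

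The two selective mechanisms push the change contrast in opposite directions. When low scorers leave from baseline onwards, those who remain started higher, so their change shrinks while their raw 3-month mean is inflated. When poor improvers leave, change is inflated. In a separate run with correlation 0.5, dropout depending on the post score alone left the change contrast unbiased.

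**What the likelihood analysis does.** In simulations of 88 participants, a likelihood analysis using all observed data gave 0.42 to 0.43 under both selective mechanisms. With random dropout both methods were unbiased, and the standard errors differed by roughly 1–7% in favour of the likelihood analysis (for example 0.229 against 0.221, and 0.243 against 0.225).

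**The case against.** Several objections have force.

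- **The follow-up sentence does not say repeated-measures.** That is so. A reader might infer that someone who missed only the 3-month email is removed at every time point. This follows only if one wide-format four-level ANOVA is fitted. The phrase also fits several separate analyses, and such a person would then stay in the 2-week one. Under either reading, though, only responders are analysed.
- **The intention-to-treat sentence may cover all outcomes.** It is not expressly limited to pre-post. But the follow-ups have their own sentence, which names only ANOVA. If the mixed model was meant to apply there, that sentence needs the same correction.
- **A complete-case pre-post ANOVA is also planned.** Correct, so a follow-up ANOVA has a counterpart. What is missing is the follow-up counterpart of the intention-to-treat analysis.
- **Attrition is not stated to be greatest at follow-up.** A reader might infer it from the three reminders, but a reminder is also planned for the second assessment and no rates by wave are given.
- **Maintenance is exploratory.** Yes. The separately planned pre-post comparisons are not affected.
- **Controls may be treated before follow-up.** This stands. The simulation's maintained difference against an untreated control need not exist in this trial, and a mixed model does not restore that comparison.

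**Conclusion.** The point holds as an inconsistency in method that is cheap to remove. The plan ties the 2-week and 3-month data to an analysis of responders, while adopting a better method under missing-at-random for missing data in the same section.

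Its size cannot be fixed from the document. Under the assumed losses, a single four-wave listwise ANOVA would use about 64, 56 or 47 of 88 people. With selective dropout, illustrative estimates of a true 0.43 SD run from about 0.38 to 0.71. A reader might infer that the ANOVA understates (or overstates) maintenance, but neither direction is supported: the sign depends on the dropout mechanism and the contrast. With random dropout there is no bias and the loss of precision is small. The advantage of the mixed model rests on missing-at-random, which the plan already assumes.

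The consequence is confined to the exploratory maintenance result.

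**What to change.** Replace the follow-up sentence with a REML mixed model for AST-D-II, DASS-21 and PHI at pre, post, 2 weeks and 3 months. Include group, time and group-by-time, with an unstructured covariance, in all randomised participants with any observation. Report the ANOVA only as a complete-case sensitivity analysis, saying whether it is one model over all waves or one per wave, and give the number analysed per arm at each wave.

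Add a sentence saying that, because controls may take the programme right after the second assessment, the follow-up group contrast is not programme against an untreated waiting list under either method.

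The cost is two or three sentences and one extended model in a procedure that the intention-to-treat analysis already needs. No new data are required. As the Trial status section reports the study completed, the change should be dated and reported as a change to the published plan.
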